## Background

Acute stroke in pregnancy and puerperium (ASPP) is a rare but serious complication associated with high morbidity and mortality in women of childbearing age. The incidence of pregnancy-associated stroke is estimated at 30 per 100,000 pregnancies and appears to be rising, with an inhospital mortality rate of 4.2% for pregnant women experiencing acute stroke [1–3]. Compared to their nonpregnant counterparts, pregnant women with acute stroke face a higher risk of deterioration and more complex management needs [4]. Regarding the long-term risk of ASPP, women with pregnancy-associated stroke have lower risks of recurrent ischemic stroke and mortality compared to those with strokes unrelated to pregnancy. Furthermore, the risks of recurrent intracerebral hemorrhage and cerebral venous thrombosis do not differ significantly, and recurrent stroke during subsequent pregnancies remains rare [5].

Previous studies have predominantly utilized large-scale national healthcare data and the International Classification of Diseases (Tenth Revision, Clinical Modification) (ICD-10-CM) to examine the incidence rate and risk factors for ASPP [6–8]. Although these population-based studies benefit from larger sample sizes, they often lack detailed data, which hinders a comprehensive exploration of risk factors and the identification of prognostic predictors and range of variables collected, such as laboratory results, neuroimaging characteristics, and management strategies. This limitation hampers the comprehensive exploration of risk factors and the identification of prognostic predictors. As women with ASPP are generally young and likely to achieve good recovery, no long-term follow-up studies have been conducted to assess their long-term functional outcomes. Additionally, it remains to be explored whether ASPP is solely a short-term risk factor that does not affect a woman’s risk of stroke in future pregnancies or throughout her life.

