## Methods

### Design

This is a retrospective, observational, nationwide, multicenter study divided into three parts. The first part is a case-control study aimed at identifying the risk factors of ASPP and its prognostic predictors. The second part is a cohort study to evaluate the impact of ASPP on the risk of recurrent stroke. The third part is a cohort study to assess the impact of ASPP on the prognosis of their offspring.

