**Fig. 1 Fig1:**
[figure not shown]
The geographical distribution of centers participating in the ASPP study. The ASPP study aims to include 36 territorial or regional centers across 22 provinces in China

ASPP patients and non-ASPP participants from January 2015 to November 2024 will be included (Fig. 2). Table 1 lists the inclusion criteria and exclusion criteria. ASPP patients are defined as those who experience acute stroke events during pregnancy or within 6 weeks postpartum, confirmed by neuroimaging evidence of cerebral infarction or hemorrhage corresponding to their symptoms.

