Grouping of non-ASPP participants is as follows:Non-ASPP participants include two matched control groups: The first group consists of participants in the pregnancy or postpartum period without a history of stroke (pregnancy/postpartum non-stroke group); the second group consists of nonpregnant or non-postpartum participants who have recently experienced a stroke (nonpregnant stroke group).Matching criteriaFor the pregnancy/postpartum non-stroke group, controls will be matched to ASPP cases in a 1:1 ratio based on age (±2 years) and hypertension history, with the latter stratified into preexisting hypertension, pregnancy-induced hypertension, or no hypertension.For the nonpregnant stroke group, a 1:1 matching strategy will be applied using age (±2 years), stroke etiology (classified by TOAST criteria), and preexisting hypertension status.Classification of pregnancy-related etiologies is as follows:Postpartum vascular diseasePregnancy-related hypercoagulable statesPregnancy-induced hypertensionPreeclampsiaAmniotic fluid embolismMatching of nonpregnant/postpartum patientsAge matching (±2 years)Matching based on stroke etiology, such as cardiogenic stroke, atherosclerotic stroke, small vessel disease stroke, and other identifiable causes (e.g., intracerebral hemorrhage)Health status and comorbidities, including common comorbidities such as cardiovascular disease, hypertension, and diabetesLifestyle factors, such as smoking and alcohol consumption historyDiscussion of the impact of pregnancy-related etiologiesEtiological characteristics, such as thrombosis resulting from pregnancy-related hypercoagulable states, hemodynamic changes caused by postpartum vascular disease, and hypertensive lesions associated with preeclampsiaPhysiological changes: Physiological changes during pregnancy, such as increased blood volume, blood pressure fluctuations, and alterations in coagulation mechanismsPsychological and social factors: Assessing the unique challenges faced by pregnant women in coping with stress, anxiety, and other mental health issues, as well as their potential impact on stroke occurrenceImpact assessment: When comparing ASPP patients with nonpregnant stroke patients, the influence of pregnancy-related etiologies on stroke recurrence rates and long-term prognosis will be clearly delineated.

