**• Medication history**
▪ Antihypertensive (if with record the duration of antihypertensive medication use, including pre-pregnancy and during pregnancy, and the types of medications, such as methyldopa, labetalol, amlodipine)
▪ Antiplatelet
▪ Oral contraceptive
• **Stroke evaluation**
▪ Type: Ischemic (thrombotic, embolic) or hemorrhagic (intracerebral, subarachnoid)
▪ Etiology
(1) Ischemic stroke (carotid stenosis, intracranial atherosclerotic stenosis, cardiogenic embolic stroke, arterial dissection, pregnancy-related hypercoagulable state, moyamoya disease)
(2) Hemorrhagic stroke (AVM, IA, pregnancy-related hypercoagulable state)
(3) Other stroke types: Cerebral venous thrombosis, cerebral sinus thrombosis, stroke caused by systemic inflammation, hematological disorders (such as thalassemia, aplastic anemia), arterial dissection (such as carotid dissection), cardiovascular diseases (such as valvular heart disease, embolism due to atrial fibrillation)
▪ Location and size: Anterior or posterior circulation, cortical or subcortical
▪ Diagnostic neuroimaging: CT, CTA, MRI, MRA, DSA, etc.
▪ Cardiac examination: ECG, echocardiography, etc.
• **Pregnancy-/puerperium-associated variables**
▪ Week of gestation and trimester at stroke onset^a^
▪ Gestational hypertension
▪ Preeclampsia/eclampsia
▪ HELLP syndrome
▪ Gestational diabetes
▪ Frequency of previous pregnancy and pregnancy-/puerperium-associated stroke
• **Data on delivery**
▪ Type: Spontaneous vaginal delivery, cesarean section, or prenatal termination (induced abortion or labor)
▪ Week of gestation at delivery
• **Stroke management**
▪ Ischemic stroke
(1) Nonsurgical treatment (if with record dose and duration): anticoagulant (heparin, warfarin), antiplatelet (aspirin, clopidogrel), intravenous thrombolysis (alteplase, tenecteplase), etc.
(2) Surgical treatment: mechanical thrombectomy, etc.
▪ Hemorrhagic stroke
(1) Nonsurgical treatment: Supportive (blood pressure control, intracerebral pressure control), etc.
(2) Surgical treatment: Open surgery (clipping for IA, excision for AVM, hematoma evacuation), endovascular intervention (coiling for IA, embolization for AVM), ventriculopuncture drainage, etc.
▪ Time relationship with terminating the pregnancy (if with surgical treatment): after, before, or during the same period
• **Complications**

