### Statistical analysis

Descriptive statistics will express continuous variables as means (±standard deviation) or medians (interquartile range) and categorical variables as proportions. Chi-square tests or Fisher’s exact tests, along with Student’s *t*-tests or Wilcoxon rank-sum tests, will be used to compare demographics and clinical characteristics between cases and controls. Chi-square tests will compare dichotomous outcomes, while *t*-tests or Mann-Whitney *U*-tests will compare quantitative outcomes. Kaplan-Meier curves and log-rank tests will evaluate survival analyses, with Cox proportional hazard models calculating hazard ratios and 95% confidence intervals (CIs). Multivariate logistic regression will identify independent predictors, and linear or generalized linear models will assess the impact of ASPP and other factors on delivery outcomes and the ASQ-3 results. First, logistic regression will calculate odds ratios and 95% CIs for recurrent stroke. Subgroup analysis will evaluate potential differences in endpoints for predefined subgroups (such as gestational hypertension, preeclampsia, HELLP syndrome, gestational diabetes, trimester, and type of delivery). Multiple imputation will address missing baseline data, with a *p*-value of < 0.05 considered statistically significant.

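### Aim 1 risk-factor comparison: non-stroke controls have no gestational or postpartum index time, so conditions that arise during pregnancy are not compared over a common window

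*Protocol article*

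**What the plan says.** All references are to the protocol article.

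- **Purpose.** The Design section states: "The first part is a case-control study aimed at identifying the risk factors of ASPP and its prognostic predictors".
- **Cases.** Under Participating centers and patient population, cases are "those who experience acute stroke events during pregnancy or within 6 weeks postpartum".
- **Controls.** The first control group is "participants in the pregnancy or postpartum period without a history of stroke". The text under the matching criteria says that "controls will be matched to ASPP cases in a 1:1 ratio based on age (±2 years) and hypertension history". Hypertension history has three levels there: present before pregnancy, arising in pregnancy, or absent. Gestational week, trimester, antenatal or postpartum status and an index date are not among the matching factors.
- **Variables.** Table 2 includes "Week of gestation and trimester at stroke onset", a time that exists only for women with a stroke. Gestational hypertension, preeclampsia/eclampsia, HELLP syndrome and gestational diabetes are listed without a diagnosis date or cut-off. The Data collection section says that pregnancy-associated variables are also collected for participants without ASPP, and names no reference time.
- **Analysis.** The Statistical analysis section plans multivariable logistic regression for independent predictors. It mentions neither an index time nor a restriction to exposures that precede the stroke.

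**The concern.** A case-control odds ratio has a clear meaning only if exposure is ascertained up to comparable points in cases and controls. Here the case's clock can stop at stroke onset, possibly early in pregnancy, and nothing stops the control's clock. For a condition that appears as gestation advances, there are two ways to proceed, and both are faulty:

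1. **Cases are cut at onset and controls are seen through delivery.** Cases have had less time to acquire the condition, so its odds ratio is pushed down.
2. **Both groups are recorded over the whole pregnancy.** Conditions first diagnosed after the stroke count as if they preceded it, so the odds ratio can be pushed up.

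The matching rule carries the same gap, because pregnancy-induced hypertension develops during gestation and the stratum has no as-of time. A case can be classified at onset and her control over a whole pregnancy.

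At stake is the interpretation of the pregnancy-specific candidates, chiefly gestational diabetes, preeclampsia/eclampsia and HELLP syndrome. Enrolling more women would not remove the bias.

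**Working it through.** The plan states no figure for this bias, so there is none to reproduce. The document gives neither the distribution of onset times nor the prevalence of the exposures. Every input below is therefore assumed, except the group size of 400 v 400, which is in the Abstract. The true odds ratio is set to 1 throughout.

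**A. Cases cut at onset, controls seen through delivery**

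Let p be the prevalence in controls by delivery and s the share of cases whose stroke precedes any possible diagnosis. Recorded case prevalence is q = p × (1 − s), and OR = [q/(1 − q)] / [p/(1 − p)].

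- p = 0.15, s = 0.20: q = 0.12; OR = 0.1364/0.1765 = 0.77.
- p = 0.15, s = 0.30: q = 0.105; OR = 0.1173/0.1765 = 0.66.

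A second form lets the condition accrue gradually. Let P be whole-pregnancy prevalence, a the share of strokes with antenatal onset, and f the share of eventual exposure already present at onset. Then q = P × (a × f + 1 − a). With P = 0.10:

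| a | f | q | Null OR |
|---|---|---|---|
| 1.0 | 0.50 | 0.050 | 0.47 |
| 0.4 | 0.25 | 0.070 | 0.68 |
| 0.4 | 0.75 | 0.090 | 0.89 |
| 0.2 | 0.75 | 0.095 | 0.94 |

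In a simple comparison of 400 v 400 that ignores the matching, the first row would be declared significant at 0.05 about 77% of the time and the second about 33%. The bias shrinks as more strokes are postpartum or as more of the exposure is present by onset.

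**B. Whole pregnancy counted in both groups**

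Let g be the share of cases unexposed at onset in whom the condition is first recorded after the stroke. With 10% exposed at onset and 10% in controls, q = 0.10 + 0.90 × g.

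- g = 0.02: q = 0.118; OR = 1.20.
- g = 0.05: q = 0.145; OR = 1.53.
- g = 0.10: q = 0.190; OR = 2.11.

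**C. With a shared index time**

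If each control is cut at her case's gestational week or postpartum day, the reduction in A applies to both groups. With p = 0.15 and s = 0.20, the comparison is 12% v 12%, so the OR is 1.00. Diagnoses made after the index, as in B, are excluded from both groups.

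A and B are alternatives for any one exposure. The document does not say which applies, so the direction cannot be stated.

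**The case against.** The best defence is that this is a condensed article. Diagnosis dates and an exposure cut-off could stand in the case report form or the full protocol, and their absence here is only silence. That is fair for the cut-off. It does not answer the matching rule, which is set out with a caliper and strata and leaves controls without a time at which any cut-off could apply.

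Three further points stand and limit the concern. Pregnancy-induced hypertension is a matching factor, so gestational hypertension is balanced by design and related disorders may be partly balanced. What remains is that the stratum is undated. Factors settled before pregnancy, such as prepregnancy BMI and migraine, are unaffected, and antenatal conditions in postpartum strokes are affected little. The primary outcomes are functional status, recurrence and offspring measures, none of which is a risk-factor odds ratio.

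A reader might also infer more than the text supports:

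- **Cesarean delivery caused by the stroke would appear as a risk factor.** The Statistical analysis section models delivery as an outcome of ASPP and otherwise uses type of delivery only as a subgroup. No analysis of it as an exposure is described.
- **Laboratory values are taken after onset in cases and at arbitrary times in controls.** Table 2 gives no draw times for either group, and the text does not clearly say that controls have these values.
- **The trimester subgroup is unworkable.** It can be run among cases alone, for differences in their endpoints.
- **Table 2 records no timing except that of the stroke.** It also lists admission and discharge dates, week of gestation at delivery and birth date. What is missing is a counterpart to onset for controls.

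**Conclusion.** The concern holds in a limited form. As written, the comparison with non-stroke pregnant or postpartum controls gives controls no index time. Gestational diabetes, preeclampsia/eclampsia and HELLP syndrome are therefore not compared over a common window, and the pregnancy-induced hypertension stratum is undated.

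Under the assumed inputs, a null odds ratio becomes 0.77 to 0.66 in the simple illustration. It ranges more widely, on either side of 1, under the other assumptions shown. These values show that the bias can matter; they do not estimate it, because both its size and its direction depend on an onset distribution and a cut-off that the document does not give. It would be wrong to conclude that all Aim 1 risk factors are biased, or that the primary outcome analyses are undermined. This is a correctable weakness in one part of the study and worth repairing before the risk-factor analysis is run.

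**What to change.** - **Index time.** Under the matching criteria, give each non-stroke control an index time equal to her matched case's gestational week or postpartum day at onset. Require that she was still pregnant or in the puerperium, and stroke-free, at that time. This can be part of the matching, or be assigned within existing pairs when the data are abstracted.
- **Dates.** Abstract diagnosis dates for gestational diabetes, preeclampsia/eclampsia, HELLP syndrome and pregnancy-induced hypertension from the electronic records already being read.
- **Matching stratum.** Classify pregnancy-induced hypertension as of the index in both members of the pair.
- **Exposure rule.** For the risk-factor analysis, count only conditions dated on or before the index in both groups.

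The cost is a short amendment, extra date abstraction and a somewhat smaller pool of eligible controls. If the index is assigned within existing pairs, some pairs may need a replacement control, because the woman was not eligible at that time or because dated hypertension status changes her stratum.

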The findings of this study should be interpreted within the context of potential limitations. Firstly, this is a retrospective study, which is subject to several inherent biases, such as recall and information bias, potentially jeopardizing its validity. Secondly, follow-up via telephone interviews may lead to a high dropout rate. Thirdly, concerns among ASPP patients regarding the privacy of their offspring’s information may result in a significant number being unwilling to cooperate, leading to selection bias. To address these issues, expanding the sample size by including more centers would be an effective solution for achieving statistical validity. Finally, although this study focuses on the Chinese population and mainly includes the Han ethnic group as the primary ethnic cohort, it employs two methodological measures, geographical heterogeneity and biological consistency, to ensure the generalizability of the research findings. The study included 22 provinces representing different socio-economic and medical resource conditions to ensure geographical heterogeneity. According to previous national studies, in the Chinese population, the key risk factors for ASPP, such as hypertension and coagulation dysfunction, show minimal differences across different ethnic groups, suggesting that the study subjects have biological consistency [24, 25].

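### Matching the pregnant controls on hypertension, and requiring them to be free of prior stroke, makes both factors unestimable as risk factors for ASPP; the etiology-matched group cannot show what pregnancy-related etiologies contribute to the recurrence difference

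*Protocol article*

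**What the plan says.** The Design section states: "The first part is a case-control study aimed at identifying the risk factors of ASPP and its prognostic predictors". The recurrence part is separate: "The second part is a cohort study to evaluate the impact of ASPP on the risk of recurrent stroke".

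The grouping and matching text in Methods defines two control groups.

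- **Pregnancy/postpartum non-stroke group.** These are "participants in the pregnancy or postpartum period without a history of stroke". For matching, "controls will be matched to ASPP cases in a 1:1 ratio based on age (±2 years) and hypertension history". The hypertension factor has three levels: present before pregnancy, induced by pregnancy, or absent.
- **Nonpregnant stroke group.** Here "a 1:1 matching strategy will be applied using age (±2 years), stroke etiology (classified by TOAST criteria), and preexisting hypertension status". A second list in the same text adds other comorbidities, smoking and alcohol. The abstract mentions only age and/or stroke etiology for the matching and does not mention hypertension.

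For the comparison of ASPP patients with nonpregnant stroke patients, the article promises that "the influence of pregnancy-related etiologies on stroke recurrence rates and long-term prognosis will be clearly delineated". The limitations paragraph of the Discussion refers to "the key risk factors for ASPP, such as hypertension and coagulation dysfunction". Nothing in the article sets hypertension aside as a factor not to be studied.

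**The concern.** Matching in a case-control study fixes the distribution of the matching factor in controls to that of the cases, so the data then carry no information on that factor's main effect. Here the factor is one that the article itself calls key, in the part of the study meant to find risk factors. A reader could take an odds ratio near 1 for hypertension as evidence of no association when the selection rule produced it.

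A stroke-history restriction on one side only has a similar result for prior stroke.

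In the recurrence part the issue differs. Etiology is made equal between ASPP and nonpregnant stroke patients, yet the article wants to describe through that comparison what the pregnancy-related etiologies contribute.

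**Working it through.** The article gives no figure for hypertension that could be reproduced. The only exposure it sizes in the case-control part is high parity (1.45-fold). The check is therefore structural, with numbers to illustrate it. Exposure, etiology and recurrence frequencies below are assumptions; 400 per group is the article's figure.

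**1. Hypertension, pregnant controls.** Assume control frequencies of 0.90 (none), 0.03 (preexisting) and 0.07 (pregnancy-induced), and a true odds ratio of 4 for both hypertensive levels.

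- Case weights: 0.90, 0.03 × 4 = 0.12 and 0.07 × 4 = 0.28, summing to 1.30.
- Expected cases of 400: 276.9 none, 36.9 preexisting, 86.2 pregnancy-induced.
- Controls matched as written have the same counts. Crude OR = (86.2 × 276.9)/(276.9 × 86.2) = 1.00.
- The conditional OR is the ratio of the two kinds of discordant pair. Both counts are 0, so it is 0/0, undefined.
- Controls matched on age only: 360, 12 and 28 expected. OR = (86.2 × 360)/(276.9 × 28) = 4.00.

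Simulation over several true values, for pregnancy-induced hypertension against none:

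| True OR | Matched as written: crude OR | Discordant pairs | Age-only matching: OR |
|---|---|---|---|
| 1.45 | 1.00 | 0 | 1.46 |
| 2 | 1.00 | 0 | 2.03 |
| 4 | 1.00 | 0 | 4.10 |
| 8 | 1.00 | 0 | 8.15 |

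Power with 400 cases and 400 controls not matched on hypertension, for control prevalence from 3% to 10%: 16–39% for OR 1.45, 49–92% for OR 2, over 99% for OR 4.

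The planned logistic regression cannot restore the contrast. Nor can the other control group: it is nonpregnant and is itself matched on preexisting hypertension.

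**2. Prior stroke.** OR = (exposed cases × unexposed controls)/(unexposed cases × exposed controls). Exposed controls are 0 by definition. Cases carry no such limit: Table 1 excludes women whose stroke history is missing, not those who have one, and Table 2 records previous pregnancy- or puerperium-associated stroke. The denominator is 0, so there is no valid odds ratio.

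**3. Etiology, nonpregnant stroke controls.** Assume three etiology classes with recurrence risks of 5%, 10% and 20%, an ASPP mix of 50/30/20%, a nonpregnant mix of 70/20/10%, and a within-class ASPP risk ratio of 0.8.

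- Within ASPP, highest against lowest class: (0.8 × 0.20)/(0.8 × 0.05) = 4.0. Simulation recovers 3.99 within ASPP and 4.00 in the pooled matched cohort, so this association survives matching.
- ASPP mean risk: 0.8 × (0.5 × 0.05 + 0.3 × 0.10 + 0.2 × 0.20) = 0.8 × 0.095 = 0.076.
- Against etiology-matched controls: 0.076/0.095 = 0.80.
- Against controls with their own mix: 0.7 × 0.05 + 0.2 × 0.10 + 0.1 × 0.20 = 0.075, and 0.076/0.075 = 1.01 (simulation 1.02).

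The gap between 0.80 and about 1.01 is what runs through etiology, and matching removes it. In addition, etiologies that the article lists as pregnancy-related, such as preeclampsia and pregnancy-related hypercoagulable states, have no nonpregnant counterpart to match.

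**The case against.** Matching on an established risk factor in order to study others is a recognized choice with a known price. The Discussion remark about key risk factors concerns ethnic generalizability and does not list Aim 1 exposures. Coagulation, BMI, diabetes, migraine, smoking and cardiac disease all remain open to study, and the Aim 1 primary outcome (mRS or EQ-5D) is unaffected. This limits the damage but does not remove it: the choice is defensible only if declared, and the article does not declare it.

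Three stronger readings are tempting and not supported.

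- **That the relation of etiology to recurrence cannot be estimated.** Part 2 is a cohort with recurrence as the outcome. Matching on etiology does not fix its association with recurrence, as the working shows. Whether the ASPP contrast should include or exclude the path through etiology is a choice of estimand; the fault lies in promising what this comparison cannot give.
- **That preeclampsia, eclampsia and HELLP syndrome are matched away as well.** The article lists preeclampsia separately from pregnancy-induced hypertension, and Table 2 records gestational hypertension, preeclampsia/eclampsia and HELLP syndrome separately. Whether they fall inside the matching stratum is not stated, and contrasts within a stratum would survive if they do.
- **That a set number of the 400 ASPP patients would have no match.** The article gives no share with a pregnancy-specific etiology, so any count would be 400 times a guess.

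The second matching list may be an elaboration whose layout was lost when the text was extracted. Even so, it differs from the first list and from the abstract.

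**Conclusion.** The point holds in this form. As written, the study cannot estimate the main effect of preexisting or pregnancy-induced hypertension on ASPP: crude OR 1.00 and no discordant pairs whatever the true value. This follows from the selection rule and needs no assumed frequencies. Prior stroke is likewise not estimable, with no exposed controls by definition.

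Still estimable are contrasts inside a hypertension stratum (for example preeclampsia against gestational hypertension, if both fall in the same stratum), effect modification by hypertension, and hypertension as a prognostic factor among ASPP patients.

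In the nonpregnant group the defect is narrower. The etiology-matched contrast leaves out whatever runs through etiology, so it cannot delineate the influence of pregnancy-related etiologies. The size of that loss (0.80 against about 1.01) is only an illustration under assumed inputs.

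**What to change.** - **Pregnant controls.** Match on age only, and adjust for hypertension, which is already collected, in analyses of other factors. Where controls are already selected and followed, keep them, state that hypertension is not studied as a risk factor, and say that an odds ratio near 1 must not be read as no effect.
- **Prior stroke.** Exclude cases with prior stroke from the risk-factor analysis, or define controls as stroke-free in the index pregnancy and puerperium. Only the second option lets prior stroke be studied.
- **Nonpregnant controls.** Match on age and stroke type as recorded in Table 2. Examine pregnancy-related etiologies within ASPP patients, or against controls not matched on etiology. Adding etiology as a covariate in the group comparison would condition on the same path and bring the problem back.
- **Text.** Reconcile the two matching lists with each other and with the abstract, and reword the promise about pregnancy-related etiologies.

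Cost: hypertension is balanced by adjustment rather than exactly. Inclusion ran to November 2024 and the first follow-up round was scheduled for December 2024 to February 2025, before the article appeared in June 2025. Any re-selected controls would miss that round and would need consent. Keeping the existing controls and declaring the limit costs only text, but gives up hypertension as a risk factor.

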### Follow-up schedule

All participants will be followed up through telephone interviews. The initial follow-up is scheduled to take place between December 2024 and February 2025. The follow-up phase will consist of three rounds, each lasting 3 months and conducted every 3 years. The specific follow-up schedule is as follows:(1) First follow-up: Conducted between December 2024 and February 2025, focusing on stroke recurrence, cardiovascular health indicators, and quality-of-life assessments. During this period, any newly occurring stroke events will be documented, including the nature and severity of recurrent strokes, and changes in cardiovascular risk factors, such as blood pressure and lipid levels, will be monitored.(2) Second follow-up: Conducted between December 2027 and February 2028, continuing with telephone interviews and standardized questionnaires to assess participants’ life quality, including emotional state and daily activity capacity, while monitoring stroke and cardiovascular health status(3) Third follow-up: Conducted between December 2030 and February 2031 to further observe late-stage stroke and cardiovascular disease, particularly focusing on the increased cardiovascular risk phase post-menopause.

If participants report a stroke recurrence during the follow-up period, researchers will obtain the hospitalization records through the following process to confirm the event: First, researchers will contact the participant’s attending physician or the relevant hospital to systematically request the hospitalization records and medical information. Second, relevant medical records will be reviewed to verify the reported recurrence event, including confirmation of diagnosis, treatment course, and length of hospitalization. Additionally, if necessary, researchers will request neuroimaging assessments (such as CT or MRI) to further confirm the nature and severity of the stroke.

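### Neither matching rule includes index date or center, so a difference in index-year mix between groups would bias outcomes analyzed without follow-up time

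*Protocol article*

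**What the plan says.** The matching rules stand in Methods, under Participating centers and patient population, after Table 1. For the pregnancy/postpartum group without stroke, "controls will be matched to ASPP cases in a 1:1 ratio based on age (±2 years) and hypertension history". For the nonpregnant stroke group, "a 1:1 matching strategy will be applied using age (±2 years), stroke etiology (classified by TOAST criteria), and preexisting hypertension status". A further list for that second group adds comorbidities and lifestyle. Index date, calendar year and hospital appear in none of these lists. The second group is described only as "nonpregnant or non-postpartum participants who have recently experienced a stroke", with no link to the date of the matched case.

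On timing, the same section states that "ASPP patients and non-ASPP participants from January 2015 to November 2024 will be included". Under Follow-up schedule, "The initial follow-up is scheduled to take place between December 2024 and February 2025", and "The follow-up phase will consist of three rounds, each lasting 3 months and conducted every 3 years". The later rounds are December 2027 to February 2028 and December 2030 to February 2031.

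Statistical analysis names chi-square tests for dichotomous outcomes, linear or generalized linear models for ASQ-3, and Kaplan-Meier, log-rank and Cox methods. It also says that "logistic regression will calculate odds ratios and 95% CIs for recurrent stroke". The Aim 1 and Aim 3 primary outcomes (mRS/EQ-5D and ASQ-3) are taken at follow-up, which is a calendar window and not a set time after the event.

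**The concern.** With a ten-year intake and common calendar windows, a woman's index date determines how long she has been at risk, how long she has had to recover, and how old her child is at the ASQ-3 call. Matching is where the plan could make these equal between groups, and it fixes the factors without doing so. Controls could come mainly from recent years, when women are easier to trace and consent, and the wording for the stroke controls leaves room for that.

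The comparisons at stake differ by control group:
- **ASPP versus nonpregnant stroke controls:** recurrence, where it is compared as a proportion, and functional status at follow-up.
- **ASPP versus pregnant/postpartum controls:** ASQ-3 and, where compared, functional status. These controls have no stroke history, so recurrence does not arise for them.

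Hospital is a second unmatched factor. It could matter through local care and record quality, but the document gives nothing with which to size it.

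**Working it through.** The plan gives no figure for this point, so there is none to reproduce. The dates come from the document. The recurrence rates and the shifts in index date are assumptions.

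**Spread of follow-up.** Intake spans 9.9 years. The shortest gap to round 1 is 1 day (30 November to 1 December 2024). The longest is about 10.2 years (1 January 2015 to 28 February 2025). At mid-window the range is about 3.1 to 13.0 years at round 2 and 6.1 to 16.0 at round 3. Even intake gives a mean of about 5 years at round 1, hence about 8 and 11 at rounds 2 and 3.

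**Logistic odds ratio under no effect.** With the same constant rate h in both groups, risk by time t is 1 − exp(−ht), so the odds are exp(ht) − 1. If controls are indexed d years later on average, OR = [exp(ht) − 1] / [exp(h(t − d)) − 1].

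Round 1, d = 1:
- h = 0.01: 0.05127 / 0.04081 = 1.256
- h = 0.05: 0.28403 / 0.22140 = 1.283

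Round 1, d = 2:
- h = 0.01: 0.05127 / 0.03045 = 1.684
- h = 0.05: 0.28403 / 0.16183 = 1.755

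The same formula at each round, for h = 0.01 to 0.05:

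| Round (mean years) | Controls 1 year later | Controls 2 years later |
|---|---|---|
| 1 (5) | 1.26–1.28 | 1.68–1.76 |
| 2 (8) | 1.15–1.17 | 1.35–1.41 |
| 3 (11) | 1.11–1.13 | 1.23–1.29 |

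If the controls were earlier instead of later, the bias would run the other way.

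**False positives.** This null simulation used 400 per group, 4,000 runs, ASPP follow-up uniform up to 10 years and a rate of 2% to 3% per year. It compares a crude test of proportions with a person-time rate test.

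| Controls | Crude OR | Crude test, false positives | Person-time test |
|---|---|---|---|
| Matched on index year | 1.00 | 4.0–4.3% | 4.4–4.7% |
| Unmatched, same year mix | 1.00 | 4.4–4.9% | 4.4% |
| Unmatched, mean 4.0 years | 1.26–1.27 | 14–19% | 4.8–5.1% |
| Unmatched, mean 3.4 years | 1.53–1.54 | 37–47% | 4.0–4.6% |
| Unmatched, mean 2.5 years | 2.05–2.08 | 71–86% | 4.4–5.1% |

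The distortion therefore needs both a difference in year mix and an analysis that ignores follow-up time.

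**ASQ-3.** The article gives the instrument's range as 1 to 66 months. At mid-January 2025, 66 months reaches back to mid-July 2019. With births even over intake, about 5.4 / 9.9 ≈ 0.55 of children fall within the upper limit at round 1. A different year mix therefore changes which children can be assessed as well as their ages.

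**The case against.** The strongest reply is that the bias is conditional. A reader might infer that the group contrasts are already confounded by follow-up length and hospital. The document does not support that: cases and controls share one intake period and the same 36 centers, and nothing says their year or center mix differs. With the same mix, the crude odds ratio is 1.00. The description of the stroke controls may mean only an incident stroke within the intake period, not a late calendar date. This stands, so the point is an uncontrolled risk.

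Second, Kaplan-Meier and Cox methods are planned, and these deal with unequal follow-up for recurrence. This also stands. The odds ratios above apply to the logistic and chi-square comparisons only, and they are largest at round 1. Prognostic predictors sought among ASPP patients alone do not depend on how controls are matched.

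Third, on hospitals, a reader might infer that the protocol admits its centers are unlike. The Discussion speaks of "22 provinces representing different socio-economic and medical resource conditions", which describes provinces. Methods describes tertiary hospitals with stroke care certification, standardized data collection and trained Apgar assessors. The quota rule balances enrollment across centers and does not pair a control with a case in the same center, so center remains uncontrolled by design, but no size can be put on it.

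Fourth, adjustment can replace matching, and covariates are commonly left to an analysis plan that is not shown. That is fair as regards the models. The matching factors, however, are fixed in the article, as is the use of logistic regression for recurrence. Adjustment also works poorly if the groups' index years barely overlap.

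**Conclusion.** The point holds as a correctable design weakness. Neither matching rule includes index date or center, while fixed calendar windows make index date the sole determinant of time at risk and child age. If the index-year mix differs, logistic or chi-square comparison of recurrence against nonpregnant stroke controls is biased, with a null odds ratio at round 1 of 1.26 to 1.28 for a 1-year shift and 1.68 to 1.76 for a 2-year shift. These figures assume a constant, equal recurrence rate of 1% to 5% per year and a mean of 5 years' follow-up. The document supplies neither the rate nor any evidence of a shift.

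Functional status at follow-up and ASQ-3 are exposed in the same way, but their bias cannot be quantified from the document. The Cox analysis is not affected by follow-up length, although it does not by itself remove differences between centers. The center part is a reason for caution only. The change is worth making because it costs little.

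**What to change.** **Matching.** Add index date (stroke or delivery, about ±1 year, nearest date first) to the 1:1 matching for both control groups. Prefer a control from the same center, and widen to province or region where none is available. State what counts as a recent stroke in the nonpregnant group, relative to the matched case's index date.

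**Analysis.** Make Cox the lead model for recurrence in place of logistic regression. Adjust mRS/EQ-5D for time since index and ASQ-3 for child age. Include center as a stratum or random effect.

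**Cost.** Admission and birth dates are already among the baseline variables in Table 2, and center is known from the source record. The price is a wider control search and some looser matches, mainly for stroke controls, who must also match on age, etiology and hypertension. A strict same-center rule is not advised. Cases average 400 / 36 ≈ 11 per center, the article does not give the number of eligible stroke controls per center, and unmatched cases would bring selection of their own. Where controls have already been chosen, use the adjustment alone and report the index-year and center distribution of each group.
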